### Interventions

2.3

This trial use 2 interventions groups and a placebo group. One of the intervention groups will receive 14,000 IU of cholecalciferol oral supplementation per week, and the other intervention group will receive 28,000 IU of cholecalciferol oral supplementation per week. The active compound is cholecalciferol (vitamin D3) from a pill containing 7000 IU per unit (SanyD) already existing in the Brazilian market (Aché Laboratórios Farmacêuticos S.A., São Paulo, Brazil).

For the double-blind masking of the groups, the vitamins were distributed as capsules; the encapsulation process was carried out by Amphora specialized handling pharmacy. Inside each capsule, the pills were intact to maintain the phycochemical integrity of the active compound. The placebo group's capsules contained only the inert formulation with the same color, smell, and weight of the other capsules distributed to the intervention groups.

Participants were individually instructed, by the responsible team, to take 1 capsule per week, preferably close to the time of eating large meals (lunch/dinner) or foods containing fat. The delivery of the capsules was carried out every 2 months with support from the company's medical team to accommodate the varied to work shifts and workplaces. Each participant has received a bottle, identified by the name of the participant, containing capsules for 10 weeks at each follow-up visit, with the last bottle containing capsules for 12 weeks, completing 52 weeks of intervention.

Compliance is ascertained by interview at follow-up visits and by phone, or participants’ message to the responsible team. To improve adherence, the responsible teams send a message every week for participants to remember to take the pill, also send messages with information about healthy lifestyle, and deliver the lipids tests results to participants after follow-up visits every 4 months.

### Outcome measures

2.4

The primary outcome to be evaluated is an 18% reduction in hypertriglyceridemia (≥150 mg/dL) between the pre and postintervention measurements. The secondary outcomes to be evaluated are a 36% reduction in hypertriglyceridemia (≥150 mg/dL) between the pre and postintervention measurements with 28,000 IU of vitamin D; an 18% reduction in high LDL cholesterol (≥130 mg/dL) between the pre and postintervention measurements; an 18% reduction in waist circumference (≥90 cm men; ≥80 cm women) between the pre and postintervention measurements; and a reduction in low cognitive impairment (by cognition tests) between the pre and postintervention measurements.

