Cross-sectional studies of several age groups suggest that hypovitaminosis D is associated with cardiovascular disease and risk factors, isolated or clustered, such as metabolic syndrome, waist circumference, body mass index (BMI), fasting glucose, blood pressure, total cholesterol, high-density lipoprotein (HDL) cholesterol, LDL cholesterol, and triglycerides.^[12–16]^ It is not yet clear whether there is a cause–effect relationship. There are few randomized clinical trials and with inconsistent results to provide an evidence on the benefit of vitamin D in reducing the risk of extraskeletal diseases, and most of those studies have been done in postmenopausal women^[17,18]^ (above 50 years), with normal sleep–wake rhythms. Thus, there are no data in the literature on the effects of vitamin D replacement in adult men (<60 years) who work in shifts.

Considering that there is still no consensus on the dose and time required for vitamin D replacement to generate beneficial effects in the cardiovascular profile, this clinical study aims to describe protocol to evaluate the effects of vitamin D3 supplementation at doses of 14,000 IU and 28,000 IU weekly for 12 months on the cardiovascular risk factors in a population of rotating shift workers. The hypothesis of the present study is that there will be an 18% reduction in hypertriglyceridemia (≥150 mg/dL) between pre and postintervention measurements in adult males with work activity that breaks the usual circadian cycle.

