### Sample size

2.6

The sample was calculated with the following assumptions: the percentage of hypertriglyceridemia in the group not exposed to vitamin D replacement (40%)^[23]^; the percentage of hypertriglyceridemia in the group exposed to vitamin D replacement (22%)^[11]^; and the likelihood ratio equal to 2.3^[11]^, considering 80% power and a 95% confidence level. As a result, this study requires 106 participants in each group; after adding 10% for losses, a total of 350 participants at least were enrolled. To estimate the sample size, OpenEpi software (Open Source Epidemiologic Statistics for Public Health, EUA) version 3.01, a web-based epidemiologic and statistical calculator for public health, was used.

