The analysis of primary and secondary outcomes will use an intention-to-treat (ITT) population and a per-protocol (PP) population. ITT population includes all participants for whom outcome data are available, in the group to which they were randomized, regardless of the treatment actually received. PP population excludes individuals who did not comply with the protocol. The primary and secondary outcomes, which are hypertriglyceridemia, high LDL cholesterol, waist circumference, and low cognitive impairment, will be compared separately between each treatment group and placebo, using binary logistic regression or regressão de Poisson, if the outcome is rare, 5% or less, and the relative risk (RR) is less than about 2^[47]^ for proportions (for binary outcomes), and using linear regression for differences in means (for continuous endpoints), with 95% confidence interval (CI). An analysis will be performed to check whether adjusting for age, duration of shift work, physical activity level, alcohol consumption, lower cholesterol drugs, and foods consumption (fiber, total carbohydrates, total fat, and saturated fat) has any impact on the estimated treatment effects; if it has no impact, then they will not be included in the model. Statistical analyses will be calculated using PASW (Predictive Analytics Software, SPSS Inc, Chicago, IL) version 17.0 and R software (R Development Core Team) version 3.5.1.

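### The primary outcome is worded as an 18% pre-to-post reduction with no comparator or scale, whereas the trial is sized and analysed on a between-arm difference of 40% vs 22%

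*Protocol article*

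**What the plan says.** **Outcome and hypothesis.** Outcome measures (2.4) reads: "The primary outcome to be evaluated is an 18% reduction in hypertriglyceridemia (≥150 mg/dL) between the pre and postintervention measurements". The Introduction states the hypothesis in the same terms: "there will be an 18% reduction in hypertriglyceridemia (≥150 mg/dL) between pre and postintervention measurements". The Abstract repeats the outcome. None of the three says whether 18% is relative or in percentage points, and none mentions placebo.

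**Secondary target.** The same section lists "a 36% reduction in hypertriglyceridemia (≥150 mg/dL) between the pre and postintervention measurements with 28,000 IU of vitamin D", together with 18% pre-to-post reductions for high LDL cholesterol and for waist circumference.

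**Sample size (2.6).** The inputs are "the percentage of hypertriglyceridemia in the group not exposed to vitamin D replacement (40"%) and "the percentage of hypertriglyceridemia in the group exposed to vitamin D replacement (22"%), with "the likelihood ratio equal to 2.3", "considering 80% power and a 95% confidence level". The result is 106 per group, and 350 in total after 10% is added for losses. One exposed-group rate is used, without distinguishing the two doses.

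**Analysis (3.2).** The outcomes "will be compared separately between each treatment group and placebo". The candidate adjustment variables are age, duration of shift work, physical activity, alcohol, cholesterol-lowering drugs and diet. Baseline triglycerides is not among them.

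**The concern.** A primary outcome should name the quantity that the trial estimates. Here it names an effect size instead, and attaches it to a different contrast (before versus after, within an arm) from the one used for sizing and analysis (active versus placebo, between arms).

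Two questions follow. The first is scale: 18% of 40% is a much smaller effect than 18 points. The second is contrast: a threshold on the pre-to-post change can be reached partly through change that placebo shares. Such change is possible in this trial. Raised triglycerides are one of the qualifying abnormalities (2.2), and participants receive lifestyle messages and their lipid results during follow-up (2.3). The Safety section itself gives reasons why a placebo group is needed.

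At stake is what counts as a positive result. A pre-to-post fall of 18%, a fall of 18 points, and a significant difference from placebo can give different answers on the same data.

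**Working it through.** **Inputs.** From 2.6: unexposed rate 0.40, exposed rate 0.22, 80% power, 95% confidence (taken as two-sided 5%; sidedness is not stated), 106 per group. From 2.1: 1:1:1 allocation.

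**Formulas.** With p̄ = (p1 + p2)/2:

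- n per group = [1.96·√(2p̄(1−p̄)) + 0.842·√(p1(1−p1) + p2(1−p2))]² / (p1−p2)²
- power = Φ{ [|p1−p2|·√n − 1.96·√(2p̄(1−p̄))] / √(p1(1−p1) + p2(1−p2)) }

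**1. The plan's own figure.** For 0.40 vs 0.22, p̄ = 0.31 and n = (1.96×0.654 + 0.842×0.642)²/0.18² = 102.4, so 103 per group. That is within 3% of the stated 106. A continuity correction gives 114. Using an odds ratio of 2.3 from 40% (treated rate 22.5%) gives 109. The total also agrees: 3×106 = 318, and 318×1.10 = 349.8, or 350. Power at 106 per group is 81.3%. The sized contrast is therefore between arms: 40 − 22 = 18 points, 18/40 = 45% relative.

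**2. The two scales for 18%.**

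| Reading | Treated rate | n per group for 80% | Power at 106 |
|---|---|---|---|
| 18 points | 22% | 103 | 81% |
| 18% relative: 40% × 0.82 | 32.8% | 700 | 19% |

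**3. Pre-to-post against between-arm.** Suppose the active arm starts at 40% and ends at 22%, so the stated target is met in points. The between-arm difference at month 12 equals the sized 18 points only if placebo ends at 40%. The document gives neither a baseline prevalence for the trial population nor an expected change on placebo, so the placebo rates below are assumptions.

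| Placebo at month 12 | Active at month 12 | Between-arm gap | Power at 106 |
|---|---|---|---|
| 40% | 22% | 18 points | 81% |
| 37% | 22% | 15 points | 67% |
| 35% | 22% | 13 points | 55% |
| 30% | 22% | 8 points | 26% |

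The pre-to-post result in the active arm is the same in all four rows.

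**4. The 36% target for 28,000 IU.** In points, 40 − 36 = 4% would remain. As a relative reduction, 40% × 0.64 = 25.6% would remain. This is a smaller effect than the 22% used for sizing, and it has 61% power at 106 per group. Neither result fits the single 22% assumed in 2.6.

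**The case against.** The best defence is that this is loose wording. 40 minus 22 is exactly 18, so the authors almost certainly meant percentage points, and on that reading the size is right. The 36% is twice 18 for twice the dose, which suggests one scale throughout. The phrase about pre- and post-intervention measurements may only name the time points, with the Statistical methods section supplying the contrast. Most of this stands, and it limits the finding. It does not explain a 36-point target that leaves 4%. Nor does it remove a numerical pre-to-post threshold from the definition of the primary outcome.

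Three stronger readings are tempting, and the document does not support them:

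- A reader might infer that the trial has only 19% power and needs about 700 per arm. That holds only for a literal relative reduction, which is the less likely meaning.
- A reader might infer that success will be declared on an uncontrolled fall. The Statistical methods section specifies no within-arm test and no such rule; it compares each dose with placebo.
- A reader might infer that a required comparison of 28,000 with 14,000 IU is missing. The stated aim (2.1) is to show efficacy of both doses, which the placebo comparisons address. The remarks about dose in the Abstract and Discussion are general.

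Regression to the mean is a reason why placebo might fall, but the document gives no input from which to estimate its size.

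**Conclusion.** The point holds as a mismatch between the stated outcome and the quantity sized and analysed. It does not show an underpowered trial. The 106 per group is adequate for 40% vs 22% (about 81% power, two-sided 5%).

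The mismatch of contrast remains whichever scale was meant. The stated target coincides with the powered difference only if the active arm starts at 40% and placebo stays at 40%, and the document states neither. Under the assumed placebo rates of 37% to 30%, the target could be met with between-arm power between 67% and 26%. The 36% target does not fit the sample-size assumptions on either scale.

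This should be fixed, but it falls short of a critical fault, because the placebo-controlled comparison is already specified.

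**What to change.** - Define the primary endpoint as the proportion with triglycerides ≥150 mg/dL at month 12, each dose versus placebo, adjusted for baseline triglycerides. Add that covariate to the list in 3.2.
- Move the 18 to the Sample size section as the design assumption: 18 percentage points, 40% vs 22%.
- Drop the 36% threshold. Report 28,000 IU versus placebo as a risk difference with 95% CI. An estimate of 28,000 versus 14,000 IU is an optional addition.
- Word the LDL cholesterol and waist outcomes as between-arm differences.
- Carry the same wording into the Abstract and the hypothesis in the Introduction.

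The cost is rewording and one covariate. Triglycerides are already measured at screening and used in the allocation, so no new data or participants are needed. The article reports the trial as not concluded; the change should be made before the treatment code is opened.

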### Participants

2.2

The study participants consisted of rotating shift workers from 5 units of a Brazilian iron ore mining company; all were adults aged between 18 and 60 years. The company's rotating shift schedule is 6 hours of work, followed by 12 hours of rest. All participants work 4 shifts on the following schedule: 7 PM to 1 AM, 1 PM to 7 PM, 7 AM to 1 PM, and 1 AM to 7 AM. After completing the 4-shift weekly cycle, they have a day off. The interviews and blood sample collection will occur in the workplaces.

The inclusion criteria are as follows:

25(OH)D levels <30 ng/mL (75 nmol/L)^[1]^With at least 1 of these parameters:Fasting glucose ≥100 mg/dL (5.55 mmol/L)^[19]^; HDL cholesterol <50 mg/dL (1.29 mmol/L) for women and <40 mg/dL (1.04 mmol/L) for men^[19]^;Triglycerides ≥150 mg/dL (3.88 mmol/L)^[19]^;LDL cholesterol ≥130 mg/dL (3.36 mmol/L)^[20]^;Blood pressure systolic ≥130 mm Hg or diastolic ≥85 mm Hg^[19]^;Waist circumference ≥80 cm for women and ≥90 cm for men.^[19]^

Subjects are excluded with evidence as following: malabsorption syndrome, kidney, liver, or thyroid diseases; specific drug use (anticonvulsants, corticosteroids, hormones, or vitamin and mineral supplements); or altered levels of serum creatinine, parathyroid hormone (PTH), serum calcium, or albumin. Among women, current breast feeding or pregnancy are also considered exclusion criteria.

After each visit (every 4 months), the follow-up will be interrupted if subjects evidence 25(OH)D >50 ng/mL (or 159 nmol/L) associated with altered serum calcium levels (>11 mg/dL) and with confirmation of a second test with altered serum calcium (>11 mg/dL) and PTH (<10 pg/mL) levels or evidence of vitamin D intoxication symptoms (dizziness, headache, nausea, rash, urticaria, weakness, numbness, and constipation); recent diagnosis of malabsorption syndrome, kidney, liver, or thyroid diseases; specific drug use (anticonvulsants, corticosteroids, hormones, or vitamin and mineral supplements); or participant request. In cases of interrupted due to intoxication, the code will be broken to clarify the diagnosis, only by the code keeper.

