### Data collection

3.1

The screening was performed in a population of 686 rotating shift workers; all individuals were invited to a general health assessment. All data were collected at the company's clinic through face-to-face interviews with a structured questionnaire assessment and a blood draw. The team responsible was composed of nurses, biochemists, nutritionists, and students, who were trained to collect the data before the study.

Figure 1 demonstrates all measurements that were evaluated at the screening visit, follow-up visits, and at the end of the 12-month supplementation period. At the screening visit, we are evaluating socioeconomic status, pre-existing diseases, drug use, sun exposure, lifestyle profile, quality of life, cognition (Table 2), blood pressure, biochemical data (Table 3), and anthropometrics and body composition measurements (Table 4). The follow-up visits will occur every 4 months and the supplementation delivery will occur every 2 months (it was integrated with follow-up visits). The follow-up visit procedures include blood sample collection, waist circumference measurement, and questionnaire interview. The vitamin D and lipid profile levels were quantified. The follow-up questionnaire monitors a presence of vitamin D intoxication, disease symptoms, drugs use, vitamins and minerals supplements, disease presence, treatment and others interventions during the trial, and food consumption alteration. At the end of the 12-month supplementation period, a reassessment of the general state of health was performed (Fig. 1).

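### The primary outcome is worded as a pre-to-post fall at the cut-off used for entry, which regression to the mean can produce in any arm; it should be restated as the planned dose-versus-placebo difference at 12 months

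*Protocol article*

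**What the plan says.** Section 2.4 (Outcome measures) states: "The primary outcome to be evaluated is an 18% reduction in hypertriglyceridemia (≥150 mg/dL) between the pre and postintervention measurements". The Abstract (Setting) and the Introduction's hypothesis repeat this pre-to-post form. The secondary outcomes follow it: "an 18% reduction in high LDL cholesterol (≥130 mg/dL) between the pre and postintervention measurements", an 18% reduction for waist at 90/80 cm, and a 36% reduction in hypertriglyceridemia tied to the 28,000 IU dose.

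Section 2.2 (Participants) uses the same three thresholds for entry, under the rule "With at least 1 of these parameters". The list of six includes "Triglycerides ≥150 mg/dL (3.88 mmol/L", "LDL cholesterol ≥130 mg/dL (3.36 mmol/L" and "Waist circumference ≥80 cm for women and ≥90 cm for men". Raised triglycerides are thus sufficient for entry, given low vitamin D, but not necessary.

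Section 2.7 says that the screening visit identifies eligible participants. Section 3.1 describes screening, follow-up every 4 months and a reassessment at 12 months, and mentions no baseline sample apart from screening. On interim data it says: "The follow-up visit procedures include blood sample collection, waist circumference measurement, and questionnaire interview. The vitamin D and lipid profile levels were quantified".

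Two other sections use a different contrast. Section 2.6 (Sample size) compares 40% hypertriglyceridemia without vitamin D with 22% with it. Section 3.2 (Statistical methods) compares each treatment group separately with placebo.

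**The concern.** When people are admitted partly because a reading reached a threshold, and are later classified at that threshold, some fall below it with no change in their usual level. Others cross upward, but if workers below the threshold are under-represented among entrants, the downward crossings outnumber the upward ones. The result is a fall in prevalence that owes nothing to treatment and occurs in every arm.

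A success criterion worded as a pre-to-post fall counts this artefact towards its target. A report could truthfully say that hypertriglyceridemia fell in the 28,000 IU arm from screening to month 12 and present that as meeting the stated outcome, although placebo fell by as much. The article also leaves two incompatible definitions of its primary result: a within-arm change in the Abstract, Introduction and section 2.4, and a between-arm difference in sections 2.6 and 3.2.

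**Working it through.** **1. The plan's own figure.** For 40% versus 22%, two-sided 5%, 80% power, with mean proportion 0.31:

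n = [1.96·√(2·0.31·0.69) + 0.842·√(0.40·0.60 + 0.22·0.78)]² / 0.18² = 102.4, so 103 per group.

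The stated 106 has 81% power by the same formula, and 3 × 106 × 1.10 = 349.8 gives the stated 350. The sample size therefore rests on a between-arm difference of 18 points. As a relative reduction that is 0.18/0.40 = 45%, so the 18% in the outcome matches the sample size only if read as points between arms.

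**2. Inputs for the noise calculation.** From the documents: the 150 mg/dL cut-off, 40% raised, 106 per arm. Assumed, because the documents give nothing: log-normal triglycerides, total log SD 0.5, within-person CV 15% to 30%, and a share q of workers below 150 who enter through another criterion (50% to 70%, independent of triglycerides).

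**3. Crossings with no treatment effect.** Within-person log variance is ln(1 + CV²), and the correlation between two readings is ρ = 1 − ln(1 + CV²)/0.25. With c = z(0.60) and B the bivariate normal probability that both readings exceed c:

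- downward share d = 1 − B/0.40
- upward share u = (0.40 − B)/0.60 = d × 0.40/0.60
- net fall among entrants = (0.40·d − 0.60·q·u)/(0.40 + 0.60·q) = 0.40·d·(1 − q)/(0.40 + 0.60·q)

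| CV | ρ | d | u | net fall, q = 0.7 | net fall, q = 0.5 | q = 1 |
|---|---|---|---|---|---|---|
| 15% | 0.91 | 16% | 11% | 2.4 points | 4.7 points | 0 |
| 20% | 0.84 | 22% | 15% | 3.2 | 6.2 | 0 |
| 25% | 0.76 | 27% | 18% | 4.0 | 7.8 | 0 |
| 30% | 0.66 | 33% | 22% | 4.8 | 9.4 | 0 |

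For example, at CV 20% and q = 0.5, prevalence goes from 57.1% to 50.9%. Varying the correlation directly from 0.95 to 0.6 moves d from 12% to 36%.

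**4. What each contrast does under no effect.** Simulation of 20,000 trials, 106 per arm, CV 20% to 25%, q 50% to 70%:

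- A within-arm pre/post (McNemar) test at two-sided 5% favours reduction in 12% to 39% of trials, against a nominal 2.5% in that direction.
- One untreated arm shows a relative fall of 18% or more in about 7% to 28% of trials.
- One untreated arm shows a fall of 18 points or more in about 1% or less.
- The between-arm test at 12 months rejects in 4.4% to 4.6% of trials, so it stays at or below its nominal 5%.

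**5. Would averaging months 8 and 12 be better?** Take the effect that moves a single reading from 40% to 22%, at 106 per arm and CV 20% to 25%. A single month-12 reading gives 81% power. The two-visit mean gives 84% to 86% if the full effect is present by month 8, 80% to 82% if 90% of it is, and 76% to 78% if 80% is.

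**The case against.** The strongest reply is that the analysis is already right. Section 3.2 compares each dose with placebo, section 2.8 balances the arms on these same parameters, and section 2.5 says that a placebo group is necessary. Regression to the mean falls equally on all arms. This stands. A reader might infer that the efficacy comparison is biased; step 4 shows that it is not.

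A reader might also infer that misclassification leaves the trial short of power. The documents do not show that. The 40% and 22% are plain percentages with hypertriglyceridemia, so reading noise is already within them if they come from single readings, and at those rates 106 per group delivers 81%.

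Nor can it be said that each status rests on one unconfirmed reading. The article states a confirmatory test only for the calcium and PTH safety rule, but the schedule figure and the measurement tables are not shown, and interim lipid and waist readings exist. Repeats at the same visit would not remove the selection problem in any case.

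The crossing shares are conditional on assumed variability and apply to triglycerides only. For LDL and waist the shared threshold is established, but its size has not been calculated.

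What the reply does not remove is the wording. The Abstract, the Introduction and section 2.4 still define success as a fall over time, and the 36% target is tied to one arm.

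**Conclusion.** The point holds as a defect in how the outcome is defined. The primary outcome, the hypothesis and the matching LDL, waist and 36% targets are stated as pre-to-post falls at thresholds also used for entry. Such falls can arise in any arm without an effect, and the wording disagrees with the between-arm contrast in sections 2.6 and 3.2.

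Under the assumptions of step 2, the artefact for triglycerides is a net fall of about 2 to 9 points, and it vanishes if everyone below 150 also enters. That is enough to mislead a within-arm test or a relative 18% target. It seldom reaches 18 points: about 1% of trials or fewer at CV 20% to 25%, and about 4% in the most extreme setting (CV 30%, q = 0.5).

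**What to change.** In the Abstract, the Introduction's hypothesis and section 2.4:

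- Define the primary outcome as the proportion with triglycerides at or above 150 mg/dL at 12 months, compared between each dose and placebo, as sections 2.6 and 3.2 already plan.
- Express the 18% as the planned between-arm difference in percentage points, 40% versus 22%.
- Drop the within-arm pre/post targets as success criteria, including those for LDL and waist and the 36% target, and state those outcomes as differences from placebo.
- Say that a within-arm fall from the screening value includes regression to the mean and is not evidence of efficacy.

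Classification on the mean of months 8 and 12 can be added as a sensitivity analysis only. As the primary definition it would gain 3 to 4 points of power if the full effect is present by month 8, and lose power if only 80% is. The Introduction itself says that the time needed for benefit is not settled.

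The cost is wording. The planned contrast, visits, samples and sample size do not change. Because section 4.1 reports 362 participants enrolled and the trial not concluded, the restatement should be dated and recorded as a clarification before the code is opened.
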